#### Selection of covariates

2.10.4

Covariates will be selected from baseline data or other risk variables affected by treatment. Adjusted analysis will be performed for basic demographic characteristics, body mass index, course of the disease, medical history in the last 3 months, the co-occurrence of psoriatic arthritis, baseline PASI scores, SAS scores, Zung self-assessment of Depression scores, and so on. At the time of patient enrollment to the group. This is to determine if basic conditions between the groups are comparable. Other risk factors will include the use of western medicine (immunosuppressants, biological agents, hormones, antibiotics, and so on).

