### Study design

2.1

This is a prospective, multicenter cohort study. The study was initiated in July 2019 and will end in December 2021. We plan to recruit 1521 psoriasis vulgaris patients from 14 hospitals in Beijing, Tianjin and Hebei province. All patients will be given therapies based on TCM and Conventional therapy guidelines and then followed-up for 1 year. Prior to recruitment, each participating hospital should be required to obtain ethics approval. Each participating hospital will follow a standard set of procedures. The flow chart of the study is depicted in Figure 1.

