### Sample size calculation

2.7

The sample size of this study was calculated based on the recurrence rates which is the primary outcome. According to the previous study, taking methotrexate as an example, the recurrence rate of conventional therapies is 73.7%,^[5]^ The recurrence rate of integrated Chinese Medicine is 28.6%,^[20]^ We suppose the recurrence rate of TCM group was 20%. Using non-equality test design by the PASS software, we set the α=0.05 and the power 1-β=0.8, the ratio of cases among each group is 1:1:1, the number of cases calculated is 390 in each group. We suppose a 30% of lost in the follow-up Of the study, the ultimately needed cases in each group is 507.

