#### General principles

2.10.1

SAS 9.2 software will be used for statistical analyses. Qualitative indicators will be described using frequency tables, percentages or composition ratios and quantitative indicators will be described using mean, standard deviation, median, lower quartile (P25), upper quartile (P75), minimum value (min), and maximum value (max). The hypothesis test will be a 2-sided test and will include test statistics and their corresponding *P*-values. *P* <.05 will be considered statistically significant.

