#### Non regulatory analysis

2.10.2

For the comparative analysis of 2 groups, qualitative data will be analyzed using the chi-square test, Fisher exact probability, Wilcoxon rank-sum test and CMH chi-square test. Quantitative data in line with normal distribution will be analyzed using *t*-test (homogeneity test of variance between groups, test level at 0.05, and Satterthwaite method will be used for correction when the variance is uneven). Wilcoxon rank-sum test and Wilcoxon signed-rank sum test will be used when the data is abnormally distributed.

The survival analysis will be used to compare statistical significance between the groups (for the appearance of new skin lesions). In addition, the Cox regression model will be used to adjust the impact of baseline PASI values, course of the disease, and body mass index.

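### Hospital is not named in any adjustment for this non-randomised 14-hospital cohort, so the cohort contrasts are exposed to hospital confounding and understated standard errors if treatment and recurrence both vary by hospital

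*Protocol article*

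**What the plan says.** - **Design (Protocol article, 2.1):** "We plan to recruit 1521 psoriasis vulgaris patients from 14 hospitals in Beijing, Tianjin and Hebei province". Section 2.3.2 assigns patients to the TCM, conventional or integrated cohort by the treatment they receive. Nothing balances treatment within hospital.
- **Sample size (2.7):** "we set the α=0.05 and the power 1-β=0.8, the ratio of cases among each group is 1:1:1", and "the number of cases calculated is 390 in each group". No ICC, design effect or hospital term appears; the only inflation is for loss to follow-up.
- **Cox model (2.10.2):** "the Cox regression model will be used to adjust the impact of baseline PASI values, course of the disease, and body mass index". This sentence follows one about new skin lesions. The same section lists a CMH test without naming its strata.
- **Covariates (2.10.4):** "Adjusted analysis will be performed for basic demographic characteristics, body mass index, course of the disease, medical history in the last 3 months". The sentence continues with psoriatic arthritis, baseline PASI and the anxiety and depression scores, and ends as an open list. Use of western medicines is added as a further risk factor.
- **Adjusted efficacy analysis (2.10.5):** logistic regression, propensity score matching on covariates not itemised there, and one stratification, by PASI level.
- **Where centre does appear:** the listing of enrolment and missing data (2.10.3) and the laboratory normal ranges (2.10.6).

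**The concern.** Without randomisation, the therapy a patient receives may depend partly on the hospital attended. If recurrence also differs by hospital, through case mix, PASI rating or follow-up practice, two things go wrong when the named analyses are run as listed.

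First, bias: part of a difference between cohorts is a difference between hospitals, and adjusting for BMI, disease course and baseline PASI does not remove it. Second, precision: patients of one hospital resemble each other, so standard errors that assume independence are too small, P < .05 is reached too often, and a test that allows for the correlation has less power than planned. The most exposed contrast is TCM versus integrated therapy, because its assumed difference is the smallest of the three.

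**Working it through.** **Inputs from the document.** Recurrence rates: conventional 73.7% ("the recurrence rate of conventional therapies is 73.7", in per cent), integrated 28.6% ("The recurrence rate of integrated Chinese Medicine is 28.6", in per cent), TCM 20%. Alpha 0.05, power 0.80, equal groups (2.7); two-sided tests (2.10.1: "The hypothesis test will be a 2-sided test"); 14 hospitals (2.1). **Assumed, not in the document:** the ICC, and the share s of treatment variation that lies between hospitals.

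**1. Reproduce 390.** Pooled two-proportion formula for independent patients, p1 = 0.286, p2 = 0.20, mean 0.243:

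n = [1.960 × √(2 × 0.243 × 0.757) + 0.842 × √(0.286 × 0.714 + 0.20 × 0.80)]² / 0.086² = (1.189 + 0.508)² / 0.007396 ≈ 389.2, rounded up to **390**.

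The same formula needs only 19 per group for 73.7% vs 28.6% and 13 for 73.7% vs 20%. So 390 comes from TCM versus integrated and carries no allowance for hospital.

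**2. Treatment fully follows hospital (s = 1).** Evaluable patients per hospital: m = 3 × 390 / 14 = 83.6. Design effect D = 1 + (m − 1) × ICC. Effective n per group = 390 / D, with power read from the same test at that n. Type I error of a test that ignores clustering = 2 × [1 − Φ(1.96 / √D)].

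| ICC (assumed) | D | Effective n per group | Power of a valid test | Type I error, clustering ignored |
|---|---|---|---|---|
| 0 | 1.00 | 390 | 80% | 5% |
| 0.005 | 1.41 | 276 | 65% | 10% |
| 0.01 | 1.83 | 214 | 55% | 15% |

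**3. Half of treatment variation between hospitals (s = 0.5), ICC 0.01.** The result depends on the m used.
- Counting only the two cohorts compared, m = 780 / 14 = 55.7 and D = 1 + 54.7 × 0.01 × 0.5 = 1.27: power about 70%, type I error about 8%.
- Taking m = 83.6 and D = (1 − 0.01) + 83.6 × 0.01 × 0.5 = 1.41: about 66% and 10%.

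**4. Same treatment mix in every hospital (s = 0), ICC 0.01.** D = 1 − 0.01 = 0.99: type I error 4.9% and power about 80%. No harm.

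**5. Comparisons with the conventional cohort.** Even at an assumed ICC of 0.10 with s = 1, D = 1 + 82.6 × 0.10 = 9.26 and effective n = 42. Power is still above 99% for both comparisons. The type I error formula depends only on D, so the excess in step 2 applies to them too.

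These figures assume equal hospital sizes and a normal approximation, which is optimistic with 14 clusters. They take 390 evaluable per group as the plan intends. They measure lost precision only; the confounding bias cannot be computed from the document.

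**The case against.** **Hospital is unnamed, not excluded.** The list in 2.10.4 is open, the propensity covariates are not itemised in 2.10.5, and the CMH strata are unspecified. An article may leave the handling of centre to a full protocol or SAP that is not shown. This stands in large part: a reader might infer that the plan rules hospital out, and it does not. Only the Cox list reads as closed, and it is tied to new skin lesions rather than to 6-month recurrence. What remains is that the article does name covariates, models and a stratification, and the design's main grouping factor is in none of them.

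**The document points to uniformity.** Each hospital follows standard procedures (2.1), and the Discussion mentions researcher training, a built-in formula for PASI and standardised examinations. So a reader may not infer as fact that hospitals prescribe or score PASI differently; nothing in the document says so. Equally, these measures do not show that hospitals are alike. A formula standardises the calculation but not the ratings fed into it, and patients who cannot attend are assessed online or by telephone.

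**The harm is hypothetical.** True of every figure beyond 390, since the ICC and the treatment mix are both assumed.

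**Adjustment helps least where the harm is greatest.** Also true. If each hospital used only one therapy, within-hospital matching or stratification would leave nothing to compare, and no analysis could separate hospital from treatment.

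**Conclusion.** The point holds in a conditional form. As listed, the analyses leave hospital unhandled in a non-randomised multicentre cohort. If treatment and recurrence both vary by hospital, the contrasts are confounded and the standard errors are too small. How much is unknown: the range runs from no loss, with treatments evenly mixed within hospitals, to power of about 65% to 55% and type I error of about 10% to 15% for TCM versus integrated, at an assumed ICC of 0.005 to 0.01 with treatment fully following hospital.

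Two stronger readings are not supported. One is that the sample size in 2.7 is wrong on this point: 390 reproduces exactly, and independence is an assumption that the document neither justifies nor contradicts. The other is that the whole study loses power: comparisons with the conventional cohort keep ample power under the assumed rates, although they have no protection from bias or excess type I error. This is a cheap improvement to the analysis, not a defect that undermines the design.

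**What to change.** - **2.10.4:** name hospital among the covariates.
- **2.10.5:** include hospital in the propensity score, and as a random effect or stratum in the logistic model for 6-month recurrence.
- **2.10.2:** include hospital as a stratum or random effect (shared frailty) in the Cox model. In both models a stratum removes between-hospital confounding where treatments overlap; a random effect may remove it only in part.
- **Standard errors:** cluster by hospital, with a small-sample correction for 14 clusters.
- **Reporting:** tabulate treatment by hospital, so that readers can see how much within-hospital comparison exists and how far the adjustment can be trusted.
- **Optional, 2.7:** state that 390 per group assumes independent patients.

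The cost is wording and programming. The per-centre listing in 2.10.3 shows that centre is available in the data. The downside is somewhat wider confidence intervals, and single-therapy hospitals will contribute little to within-hospital comparisons. These changes protect the validity of the estimates and tests; they do not restore 80% power for TCM versus integrated if the less favourable assumptions turn out to be true.

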#### Main outcomes

2.5.1

Recurrence rate in 6 months. Definition of recurrence: Patients have got relief psoriasis area and disease severity index score (PASI75), while the total PASI score increased to 50% of the original PASI.^[19]^

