#### Efficacy analysis (Adjustment analysis)

2.10.5

Efficacy analysis indicators will include changes in the main efficacy indicators from the initial visit (baseline) to each follow-up period.

Logistic regression analysis will be used to study the relationship between continuous dependent variables and independent variables. Influencing factors will be analyzed to determine which independent variable influences the probability of dependent variable occurrence. The decision analysis method will be used to estimate the probability of each category of the dependent variable (in the presence of a combination of various independent variables), to predict the outcome. The mixed effect of multiple covariates on treatment outcome will be adjusted using the propensity score matching method. First, we will determine if the distribution of patients with similar tendentiousness score is balanced among the groups. The distribution of patients will then be adjusted according to the tendentiousness score to calculate the effect estimation value. Stratified analysis will be conducted based on patients’ PASI score which will be divided into 4 groups based on the 4 levels of PASI score (less than 10,10–20,20–30 and more than 30).

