## Discussion

3

Psoriasis vulgaris has a high recurrence rate. The pattern of recurrence varies with each patient. Some patients will have early and frequent recurrence, while others may have long-term remission with few recurrences. Hence, patients may need maintenance treatment for an extended period of time. Psoriasis is characterized by long-term chronic course with recurrent attacks. RCTs that have been previously performed have not provided insights to preventing recurrence. However, real-world studies may have advantages to provide long-term insights. Previous publications have evaluated the clinical efficacy of biological agents for the treatment of psoriasis through retrospective real-world registration studies. However, no real-world or registration studies with regards to TCM for the treatment of psoriasis have been published in China.

This study did not include a placebo group, nor employed a blinded method. Patients in this study included elderly, children, pregnant and breastfeeding women and met the ethical requirements for enrollment in this study. With regard to the study design, we mainly focused on the Psoriasis Longitudinal Assessment and Registry^[21–23]^ (PSOLAR) and the National Central Cancer Registry of China^[24]^ (NCCR). The Psoriasis Registration Platform was designed to demonstrate, train researchers and to strictly adhere to standard operation process. In addition, it included guidelines for strict data collection and a management plan to improve data collection and transfer efficiency. The electronic case registration system is helpful to facilitate the interaction between doctors and patients. It actively monitors and collects information from diverse disease groups to improve data quality and authenticity. Data from the platform can also be easily shared. The platform meets the clinical needs and is reasonably standardize to facilitate the preservation of original medical records. These include access to BMI, PASI, and BSA indicators through an embedded formula. In addition, the platform contains drug library resources, diagnosis and treatment guidelines, to propose individualized prescriptions. Improvements in PASI, BSA and VAS scores for each patient's skin lesions can be visualized and monitored directly.

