Based on an intelligent and information-based data collection and data management platform, this study observed and followed-up on thousands of patients within a short period. Data will be analyzed after centralized integration to compare conventional therapy with that of the combination of Chinese and Western medicine treatment. Patients will be evaluated based on recurrence rate 6 months after PASI75, onset time, maintenance time, the incidence of new rashes during treatment and follow-up, World Health Organization Quality of Life Instruments/BSA/VAS scores and treatment costs. The long-term efficacy of TCM in treating psoriasis vulgaris through intelligent and information-based data collection and management will then be established and evaluated. It determined the advantages of TCM and provided real-world evidence for the long-term efficacy of TCM for the treatment of psoriasis. In addition, the platform could evaluate the mode and cost-effectiveness of psoriasis vulgaris treatment in the real world. Improvement of skin lesions, patient quality of life, recurrence rates of skin lesions and the state of anxiety and depression will also be able to be evaluated in the future. Long-term follow-ups of patients during remission and recurrence will provide clues to inducing factors and effective interventions for patient treatment. Using the multicenter registration platform to collect large amounts of standardized data within a short period will help mine and analyze long-term efficacy data of TCM for the treatment of psoriasis from the perspective of recurrence.

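### The named covariates include no measure of prior relapse frequency or remission length, so control of confounding by relapse tendency in the recurrence comparison is not assured

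*Protocol article*

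**What the plan says.** The primary outcome in section 2.5.1 is "Recurrence rate in 6 months". The Discussion makes the time origin clear by listing "recurrence rate 6 months after PASI75" among the evaluations. Patients join the TCM, conventional or integrated cohort according to the treatment they received for more than half of the course (section 2.3.2).

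Three places deal with adjustment:

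- Section 2.10.4 states the source of covariates: "Covariates will be selected from baseline data or other risk variables affected by treatment". Its named items include "body mass index, course of the disease, medical history in the last 3 months, the co-occurrence of psoriatic arthritis, baseline PASI scores", and the list runs on to "baseline PASI scores, SAS scores, Zung self-assessment of Depression scores, and so on". Use of western medicines is added as a further risk factor.
- Section 2.10.2, on the time to new skin lesions, says that "the Cox regression model will be used to adjust the impact of baseline PASI values, course of the disease, and body mass index". That list has three items and no opening for more.
- Section 2.10.5 says: "The mixed effect of multiple covariates on treatment outcome will be adjusted using the propensity score matching method".

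On the natural history of the disease, the Discussion says: "Some patients will have early and frequent recurrence, while others may have long-term remission with few recurrences".

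**The concern.** How often a patient relapsed before enrolment is a direct candidate predictor of whether the patient relapses again within 6 months. The protocol's own Discussion treats it as varying between patients. It may also influence treatment choice: patients who relapse often could be the ones moved to, or kept on, systemic or combined treatment. A variable related to both treatment and outcome confounds a non-randomised comparison, and matching or regression can balance only what is measured and entered.

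None of the named items measures it. Course of the disease most naturally means duration, and ten years of disease can contain few or many attacks. Baseline PASI gives current severity. The history item is limited to 3 months and is not said to concern relapses at all. At stake is whether a difference in recurrence between the TCM cohort and the others can be read as an effect of treatment.

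**Working it through.** **Step 1: the protocol's own yardstick.** Section 2.7 gives recurrence of 28.6% (integrated), an assumed 20% (TCM) and 73.7% (conventional), with α = 0.05 and power 0.80. Section 2.10.1 makes tests two-sided. A two-proportion normal test with pooled variance and no continuity correction, for 28.6% vs 20%, gives 390 per group, as stated. The smallest design contrast is therefore 28.6 − 20 = 8.6 points.

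**Step 2: how much a history window can tell.** Assumption: relapses occur at a constant rate r per year and the history item records them. The chance of no relapse in a window of t years is exp(−rt).

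| Relapses per year | No relapse in 3 months | No relapse in 12 months |
|---|---|---|
| 0.25 | 94% | 78% |
| 1 | 78% | 37% |
| 2 | 61% | 14% |
| 4 | 37% | 2% |

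Three months separates the types weakly, but does separate them. Twelve months does better.

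**Step 3: possible size without adjustment.** With no treatment effect, the spurious difference is (difference in share of frequent relapsers) × (difference in recurrence risk between types). Both inputs are assumed:

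- low end: 0.05 × (0.40 − 0.15) = 0.0125, about 1.3 points;
- high end: 0.30 × (0.70 − 0.15) = 0.165, or 16.5 points.

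**Step 4: what adjustment for one marker leaves.** Assumptions: attacks every 3 months (frequent) or every 18 months (rare) on average; 6-month recurrence risk 45% or 10%; frequent relapsers 60% of one cohort and 40% of the other; no treatment effect.

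- Crude: (0.60 − 0.40) × (0.45 − 0.10) = 7.0 points.
- Marker A, any attack in 3 months: 1 − exp(−3/3) = 0.63 for frequent and 1 − exp(−3/18) = 0.15 for rare relapsers. Among marker-positive patients the frequent share is 0.861 vs 0.733 (weight 0.393); among marker-negative patients it is 0.395 vs 0.225 (weight 0.607). Residual: 0.35 × (0.393 × 0.128 + 0.607 × 0.170) = 5.4 points.
- Marker B, at least two attacks in 12 months: 1 − exp(−m)(1 + m) with m = 12/3 = 4 or 12/18 = 0.667 gives 0.91 and 0.14. The frequent shares are 0.904 vs 0.808 (weight 0.526) and 0.138 vs 0.067 (weight 0.474). Residual: 0.35 × (0.526 × 0.097 + 0.474 × 0.072) = 3.0 points.

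Other assumptions, residual in points:

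| Change from the base case | Marker A | Marker B |
|---|---|---|
| Base case | 5.4 | 3.0 |
| Risks 40% vs 15% | 3.8 | 2.1 |
| Gaps 4 vs 12 months | 6.3 | 5.0 |
| Shares 55/45 | 2.7 | 1.5 |
| Shares 65/35 | 8.1 | 4.6 |

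With 390 per cohort and a recurrence rate of 24%, a true-null comparison carrying 5.4 points of bias would be rejected about 42% of the time, and one carrying 3.0 points about 16%. At the 27.5% average rate that the base case implies, the first figure is 39%.

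**Limits of step 4.** It adjusts for a single yes/no marker and leaves out every other named covariate, so 5.4 points is not what the planned analysis would leave. The Poisson gaps imply 6-month attack probabilities of 1 − exp(−6/3) = 86% and 1 − exp(−6/18) = 28%, while 45% and 10% are used for recurrence. An attack and a PASI-defined recurrence need not be the same event, but the two sets are not reconciled. The model also does not count the attack at presentation. If every patient enrolled in an attack and it were counted, marker A would be positive for everyone and the full 7.0 points would remain.

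**The case against.** A reader might infer that past disease is adjusted for over 3 months only, that this is too short because it is half the 6-month outcome window, and that frequent and rare relapsers therefore look alike and the comparison stays confounded. The protocol does not support that reading.

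- Course of the disease is a separate covariate with no time limit, in section 2.10.4 and in the Cox model. The 3-month limit attaches to medical history alone.
- Medical history is undefined. It could mean treatment, comorbidity or relapses, so it cannot be faulted as a failed measure of relapse tendency.
- A look-back period need not match the outcome window.
- Step 2 shows weak separation, not none. Bias also needs an imbalance between cohorts that survives matching, and the protocol gives no information on that.
- The section 2.10.4 list ends openly and draws on baseline data. The data collection table is not shown, and a full protocol or analysis plan may name relapse history.
- The 8.6-point yardstick is the smallest contrast. For conventional against integrated therapy, the section 2.7 rates differ by 73.7 − 28.6 = 45.1 points, of which 5.4 is about 12%.
- A 12-month history is no complete cure: with gaps of 4 and 12 months it still leaves 5.0 of 6.3 points.

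All of this stands, and it removes the certainty and the exact size. Three facts remain: no named item measures relapse frequency or remission length, the Cox list is closed without one, and an open ending does not commit anyone to collecting it. In a prospective study, what is not recorded at the first visit may be recoverable only by recall. If medical history does not cover relapses, the gap in the named list is wider.

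**Conclusion.** The point holds in a limited form. The covariates named in section 2.10.4 and the closed Cox list in section 2.10.2 include no measure of prior relapse frequency or remission length, although recurrence is the primary outcome, the cohorts are not randomised, and the Discussion describes patients as differing in relapse pattern. Control of confounding by relapse tendency is therefore not assured.

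The protocol does not show that bias is present, and its size cannot be computed from the document. The illustrative 1.3 to 16.5 points rests on assumed imbalances and risks. The residuals of 5.4 and 3.0 points rest on those of step 4 and a one-marker model. They show that a bias of the same order as the 8.6-point design contrast is possible and that a longer history reduces it. They are not estimates for this study.

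**What to change.** Name two baseline covariates in section 2.10.4: the number of recurrences in the 12 months before enrolment and the length of the last remission. Record both at the initial visit if they are not already collected. Enter both in the propensity score, the regression for recurrence and the Cox model in section 2.10.2. State what medical history in the last 3 months covers.

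For patients already enrolled, take the two items from records made at or before baseline where these exist. Information recalled later should enter a sensitivity analysis only: treatment is unblinded and recurrence may already have occurred, so recall may differ by treatment and by outcome.

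The cost is at most two baseline items and a few lines of protocol text. Recall of the previous year will contain some error even at the first visit, so confounding would be reduced but not removed.

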**Methods and analysis::**

This will be a prospective, multicenter cohort study. We intend to recruit 1521 psoriasis vulgaris patients from 14 hospitals in Beijing, Tianjin, and Hebei. Treatment will be based on the diagnosis specifications and clinical practice guidelines of TCM and conventional therapy. During inclusion and the subsequent follow-up period, doctors through electronic case reports will collect different therapeutic TCM regimens and conventional therapy that were administered. Information on life condition, skin lesions at each visit, World Health Organization Quality of Life Instruments, Zung Self-rating Anxiety Scale, Zung Self-assessment of Depression, laboratory examinations, incidence of new rash and recurrence during the remission and recurrence stages will be recorded.

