#### Patient cohort division

2.3.2

Patients received TCM will be classified as the TCM treatment cohort. The TCM treatment course should occupy more than half of the total course of treatment, with the following stratigies:

(1)oral herbal medicine once a day(2)external use of Chinese medicine ointment with the area of body surface area (BSA) greater than or equal to the 10% of patients’ total BSA(3)acupuncture treatment(4)external use of TCM bath.

Patients received Conventional therapy following guidelines will be classified as the Conventional therapy cohort. Conventional therapies includ: external use of drugs (Cuticle promoter and Exfoliator pledge agent, glucocorticoid, vitamin D3, vitamin A acid derivatives, immunomodulatory drugs, and so on), Internal use of drugs (antibiotics, retinoic acid, glucocorticoid and immunosuppressants, biological agents, and so on). The treatment course should occupy more than half of the total course of treatment, with the following strategies:

(1)oral use of chemical drugs(2)external use of chemical drugs ointment with the area of BSA greater than or equal to 10% of the total BSA(3)biological agents injection.

Those who meet the requirements of TCM and Conventional therapy cohort meanwhile will be classified as the integrated therapy cohort.

Study assistants will be responsible for the initial visit and follow-up of each patient. The data collection schedule is shown in Table 1.

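### The protocol does not commit to adjusting BSA, itch VAS, WHOQOL and TCM syndrome score for their own initial-visit values, and the adjusted analysis gives no model suited to them

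*Protocol article*

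**What the plan says.** Section 2.1 states the design: "This is a prospective, multicenter cohort study". Section 2.3.2 forms the cohorts from the treatment received, for example "Patients received TCM will be classified as the TCM treatment cohort". In both the TCM and the conventional cohort, ointment use qualifies only when it covers at least 10% of body surface area. The other qualifying treatments carry no area threshold. The integrated cohort must meet both sets of requirements.

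Section 2.5.2 lists BSA, itch VAS, WHOQOL and the TCM syndrome score among the secondary outcomes.

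The analysis sections then say:
- **2.10.2:** "Quantitative data in line with normal distribution will be analyzed using" a t-test, with Satterthwaite correction if variances differ and Wilcoxon tests otherwise. No covariate enters. The Cox model in the same section adjusts for baseline PASI, disease course and body mass index, but it concerns new skin lesions.
- **2.10.4:** "Covariates will be selected from baseline data or other risk variables affected by treatment". The scores that it names are "baseline PASI scores, SAS scores, Zung self-assessment of Depression scores, and so on" (SAS here is the anxiety scale).
- **2.10.5:** "The mixed effect of multiple covariates on treatment outcome will be adjusted using the propensity score matching method", followed by a balance check and stratification in four PASI bands. The only regression named in this section is logistic, although it is described as serving continuous dependent variables. The section also says: "Efficacy analysis indicators will include changes in the main efficacy indicators from the initial visit (baseline) to each follow-up period".

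**The concern.** In a cohort study the groups can differ at the start on the outcome being compared. If that starting value is not in the analysis, part of the initial difference reappears at follow-up and is read as a treatment effect. Even without imbalance, leaving it out gives up precision that the same data could provide.

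Here the text supports the concern in three ways. Treatment received decides the cohort. For BSA, an area criterion is built into one of the routes by which a patient enters a cohort. And the authors named the baselines of PASI and of the two Zung scales, but stopped before the four other scores.

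At stake are the itch, lesion-area, quality-of-life and syndrome-score comparisons. The primary recurrence outcome and the planned sample size are not affected.

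**Working it through.** **The plan's own figure.** No SD, correlation or sample size is given for any quantitative secondary outcome, so nothing on this point can be reproduced directly. The per-group number used for scale below is the 390 of section 2.7. It reproduces from 28.6% against 20%, two-sided 0.05, power 0.80, pooled variance:

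n = [1.96·√(2·0.243·0.757) + 0.8416·√(0.286·0.714 + 0.20·0.80)]² / 0.086² ≈ 389.2, rounded up to 390.

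**Assumed inputs.** Neither of these is in the document:
- correlation ρ between the initial-visit and follow-up value: 0.3, 0.5, 0.7;
- baseline difference d₀ between two cohorts: 0.2 SD.

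There is no true treatment effect, each score has unit SD, and the follow-up value depends on the past through its own baseline.

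**Formulas.**
- Bias of an unadjusted follow-up comparison: ρ·d₀.
- Variance with own-baseline adjustment (ANCOVA), relative to an unadjusted follow-up comparison: 1 − ρ².
- Standard error of the unadjusted comparison: √(2/390) = 0.0716 SD.
- Detectable difference at 80% power: 2.80·0.0716 = 0.201 SD unadjusted, multiplied by √(1 − ρ²) with adjustment.

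| | ρ = 0.3 | ρ = 0.5 | ρ = 0.7 |
|---|---|---|---|
| Bias, unadjusted follow-up (SD) | 0.06 | 0.10 | 0.14 |
| Rejection rate, nominal 5% | 13% | 29% | 50% |
| Variance, adjusted / unadjusted | 0.91 | 0.75 | 0.51 |
| Detectable difference, adjusted (SD) | 0.191 | 0.174 | 0.143 |

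The bias does not depend on the sample size; the rejection rates do.

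**What matching on PASI would remove.** Let r be the correlation between baseline PASI and the outcome's own baseline, and suppose the PASI imbalance arises through that correlation (r·d₀). The remaining bias is ρ·d₀·(1 − r²). At ρ = 0.5 and d₀ = 0.2:
- r = 0.5: 0.10·0.75 = 0.075 SD;
- r = 0.8: 0.10·0.36 = 0.036 SD.

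PASI therefore helps, most plausibly for BSA, but it does not stand in for the outcome's own baseline.

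**Change scores.** Under the same model a change-score comparison is biased by (ρ − 1)·d₀ = −0.14, −0.10, −0.06 SD. If instead the cohorts would simply keep a stable difference d₀, the change score is unbiased, ANCOVA is off by (1 − ρ)·d₀ = 0.14, 0.10, 0.06 SD, and the unadjusted follow-up comparison is off by the full 0.20 SD. Which model holds cannot be settled from the document, but in both ANCOVA is less biased than the unadjusted follow-up comparison.

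**The case against.** The strongest reply is that this is detail left open, not an error. Section 2.10.2 reads as the unadjusted half of a two-part plan, and 2.10.5 is headed as the adjusted half. Covariates may come from any baseline data and the list is open-ended. Propensity score matching, a balance check and PASI strata are all planned. A model for each secondary outcome may sit in an analysis plan that is not shown.

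Most of this stands, and it rules out several stronger readings:

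- A reader might infer that these outcomes are compared without any adjustment for their baselines. No sentence says so. The four baselines are unnamed, not excluded.
- A reader might infer that the four outcomes are analysed as change scores. Section 2.10.5 ties change only to main efficacy indicators, which it does not define, and section 2.5.1 lists only recurrence as a main outcome.
- A reader might call change scores invalid here. With non-randomised groups that goes too far, as the stable-difference case shows.
- A reader might infer that severity drives treatment choice. Section 2.3.2 does not say what drives it. The 10% area rule applies to both the TCM and the conventional cohort, so it makes a BSA imbalance plausible without proving one.

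The reply does not remove the gap in method. The tests stated for quantitative data carry no covariate, and the one regression in the adjusted section does not suit a continuous score. Section 2.10.3 mentions linear and regression models, but as responses to types of missing data, not as the between-cohort comparison of these outcomes. Matching on the named covariates also does not provide the precision gained from each outcome's own baseline.

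**Conclusion.** The point holds as a gap in commitment with a better method at hand. It does not show that the planned analysis is biased. For BSA, itch VAS, WHOQOL and TCM syndrome score, the protocol states an unadjusted test, does not name the outcomes' own baselines among the covariates, and offers no suitable adjusted model.

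The size cannot be derived from the document. With an assumed 0.2 SD imbalance and ρ of 0.3 to 0.7, the unadjusted follow-up comparison is off by 0.06 to 0.14 SD, and own-baseline adjustment reduces the variance by 9% to 49%. Matching on PASI would lower the bias by an amount that depends on an unknown correlation. Because these outcomes are secondary and the full analysis plan is not shown, this is an inexpensive improvement that should be made, not a threat to the primary conclusion.

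**What to change.** - **2.10.4:** add the initial-visit values of BSA, itch VAS, WHOQOL and TCM syndrome score to the named covariates and to the propensity model.
- **2.10.5:** state that each quantitative secondary outcome is compared between cohorts by a linear or mixed model for the follow-up value, including its own initial-visit value and the listed baseline covariates. Add a change-score analysis as sensitivity, because the cohorts are not randomised.
- **2.10.2:** keep the t-test and Wilcoxon results as unadjusted description.

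The cost is wording. No patients are added and the sample size does not change. The abstract already lists among the recorded data "Information on life condition, skin lesions at each visit, World Health Organization Quality of Life Instruments, Zung Self-rating Anxiety Scale". The data collection table is not readable in the text at hand, so the sponsor should confirm that all four scores, the TCM syndrome scale in particular, are scheduled at the initial visit.
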